#### Schedule

A flow chart detailing the pre-specified data collection time points is shown in Fig. 1 and the schedule for data collection, which will be recorded in the electronic Case Report Form (eCRF), is presented in Table 3. The observational period for each patient will begin between 4- and 72-h post-removal of the guiding catheter of a successful PCI. Patient-specific demographics and characteristics will be recorded at the time of enrolment (referred to as baseline herein; Table 3); the full list of the recorded variables is available in Supplemental Appendix SI. Patients will also be required to complete an EQ-5D-5L questionnaire at baseline to evaluate quality of life parameters.

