**Figure 1 Fig1:**

Study flow chart. *PCI* percutaneous coronary intervention.

**Table 3 Tab3:** Data collection schedule.

	Baseline	30-day Follow-up	1-year Follow-up
Date	✓	✓	✓
Eligibility	✓		
Demographics	✓		
Vital signs	✓		
Relevant medical history	✓		
Relevant concomitant diseases	✓		
Coronavirus disease-2019 status	✓	✓	✓
Relevant concomitant medication^1^	✓	✓	✓
Intake of edoxaban	✓	✓	✓
Risk factors (CHA_2_DS_2_-VASc, HAS-BLED Score)	✓		
Current status of NVAF	✓		
Creatinine, labile INR^2^	✓		
PCI details^3^	✓		
HRU parameters^4^	✓	✓	✓
PRO (EQ-5D-5L)	✓		✓
Clinical events of interest^5^	✓	✓	✓
Suspected edoxaban ADRs	✓	✓	✓

*ADR* adverse drug reaction, *ASA* acetylsalicylic acid, *HRU* health resource utilisation, *MI* myocardial infarction, *NOAC* non-vitamin K antagonist oral anticoagulant, *NVAF* non-valvular atrial fibrillation, *PCI* percutaneous coronary intervention, *PRO* patient reported outcome, *VKA* vitamin K antagonist.

^1^Relevant concomitant medication: heparin, P2Y_12_ inhibitor, ASA, NOAC, GP IIb/IIIa inhibitor, VKA, antiarrhythmic/rate control medication, NSAIDs, proton pump inhibitor, hormone therapy, P-gp inhibitor and insulin.

^2^Last available measurement in medical records (baseline or earlier).

^3^PCI Details: indication for PCI, access for PCI, number of drug-eluting stents, length, diameter and location of each stent, start date, stop date and time of procedure.

^4^HRU parameters: hospital admissions and length of hospital stay.

^5^Bleeding events, stroke, MI, PCI and death. Patients may document the events in the patient memory aid, if available. The recorded parameters, listed fully in Supplemental Appendix SI, include clinical events of interest, relevant concomitant medications, ADRs and HRU parameters.

Each patient will be followed-up at approximately 30-days (± 7 days) and 1-year (± 2 weeks) post-PCI (Table 3). Patients will be contacted by their physician by telephone to collect all relevant available information relating to the patients’ routine management between the respective data collection points. If a patient is not available, physicians are permitted to contact relatives or their primary care doctor. The recorded parameters, listed fully in Supplemental Appendix SI, include clinical events of interest, relevant concomitant medications, ADRs and HRU parameters. The quality-of-life assessment questionnaire, EQ-5D-5L, will also be collected at the 1-year follow-up.

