To facilitate complete and accurate data reporting, a structured phone interview guide will be distributed to the treating physicians prior to conducting the follow-up appointments. During the observation period, patients will have the option to complete a hardcopy memory aid diary to assist with recalling information relevant to the study at follow-up. Further, to allow for the alternative of an electronic diary, a study app for patients was developed in 2021. The patient can use the study app to document changes of the most important medications (edoxaban, clopidogrel and ASS) during the study and report clinical events of interest including hospitalisations during the 1-year follow-up period. Each patient entry can be sent to the respective study site via an email assuring that the site is immediately informed to enable immediate patient contact or to guide the structured phone interview at 1-year. The handling of data provided by the app is at the discretion of the site physician. In addition, the patient can use the app to complete the EQ-5D-5L at 1-year follow-up. These data will be automatically sent to the study database.

In the case that a patient cannot be reached at the pre-specified data collection time points (ca. 30-days and/or ca. 1-year), the treating physician is expected to repeatedly attempt to contact the patient in close proximity to the missed time point. If a patient cannot be contacted at the ca. 30-day time point, the physician is advised to continue to persistently attempt to reach the patient at the 1-year time point.

Discontinuation of edoxaban for any reason during the follow-up period will be recorded in the eCRF and at 1-year follow-up documentation by the treating physician. If edoxaban was discontinued due to an ADR, the patient must be followed-up until the ADR is resolved. Details relating to any subsequent treatment with other-than-baseline anticoagulants will be documented (i.e., type, primary cause). In the case that a patient terminates the study early, the treating physician is requested to document the primary cause for early study termination.

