##### Death

Deaths will be categorised as cardiovascular (CV) or all-cause death, with the aim of capturing the primary cause of death. Where possible, CV death will be classified in accordance with the criteria specified by the Academic Research Consortium^21^. The primary cause of death may be distinct from both the mode of death and an intervening cause that is temporally closer and contributes to the death.

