#### Statistical analysis

The patient disposition will include patients from the *All-Documented Patient Set (APS),* who have a signed and dated an informed consent form. This will summarise the number and percentage of patients in the different analysis sets including reasons for exclusion, who completed or did not complete the regular observational period (including reasons for non-completion), as well as patients who did or did not receive at least one dose of edoxaban post Index PCI. The *Baseline Analysis set* (BAS; all patients from the APS who fulfil the study eligibility criteria with any further baseline documentation) will be used to describe patient demographics and other baseline characteristics shown in Table 3 (and listed in full in Supplemental Appendix SI).

All other statistical analyses will be performed on data from the *Full Analysis Set (FAS),* consisting of all patients from the *BAS* with documentation from at least one time point post-baseline. SAS version 9.4 or higher will be used to conduct the analyses.

To address the primary objective, a descriptive analysis of data on the usage of peri- and post-procedural antithrombotic therapies, as well as other relevant concomitant medications at baseline and the two follow-up time points will be performed (to include extent of exposure and dosing regimens).

The analysis for the secondary objectives will be based on data documented for physician- and patient-reported clinical events of interest (bleeding events, stroke, MI, PCI, or death), ADRs, PROs (EQ-5D-5L questionnaire) and HRU parameters. Data for clinical events of interest will be reported as absolute and relative frequencies with 95% confidence intervals and Kaplan–Meier analyses will be performed where applicable to determine outcome risk over time. ADRs will be coded using the Medical Dictionary for Regulatory Activities coding dictionary (version 23.1 or higher) and ADR incidences will be reported. EQ-5D-5L and HRU parameters will be summarised descriptively.

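### For outcomes other than all-cause death, neither Kaplan–Meier nor a crude percentage over the FAS estimates the actual one-year risk once patients die or are lost; a cumulative incidence function would

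*Protocol article*

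**What the plan says.** The Statistical analysis section commits to two summaries of the clinical events (bleeding, stroke, MI, PCI and death). The first is descriptive: "Data for clinical events of interest will be reported as absolute and relative frequencies with 95% confidence intervals". The second is time-to-event: "Kaplan–Meier analyses will be performed where applicable to determine outcome risk over time".

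Both use the FAS, which consists of baseline-set patients "with documentation from at least one time point post-baseline". One contact is enough, so a patient reached at 30 days and never again stays in the set.

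The Schedule section provides two follow-up contacts: "Each patient will be followed-up at approximately 30-days (± 7 days) and 1-year (± 2 weeks) post-PCI". It also foresees incomplete follow-up ("In the case that a patient terminates the study early") and patients who cannot be reached, without giving an expected rate.

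Under Definitions, "Deaths will be categorised as cardiovascular (CV) or all-cause death". The article names no competing-risk method, and it states no censoring rule and no denominator rule for patients without the one-year contact.

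**The concern.** A patient who dies can no longer have a first bleed, stroke, MI or repeat PCI, and a patient who dies of a non-CV cause can no longer die of a CV cause. Kaplan–Meier in its usual form censors such patients, which treats them as still able to have the event later. One minus Kaplan–Meier then answers what the risk would be if nobody died of anything else. That is not the outcome risk the article says it wants.

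The crude percentage has the opposite weakness. A patient last seen at 30 days remains in the denominator but cannot add a later event to the numerator.

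The study has no comparator, so absolute one-year risks are its effectiveness and safety result. The Sample size calculations section judges precision on the one-year rates of major and CRNM bleeding, CV death, stroke and MI. Each of these has a competing cause of death. All-cause death, where Kaplan–Meier raises no such problem, is not on that list. A reader would be given two figures for the same outcome, displaced in opposite directions, with nothing to say which is the risk.

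**Working it through.** **Inputs from the article.** Reference event rate 17% (major or CRNM bleeding), N = 720, stated precision ±2.7 points and 16.1% relative (Sample size calculations).

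**Assumed inputs, because the article gives none.** 3% to 10% of patients die within a year without a prior event; 10% or 20% are lost after the 30-day contact; loss is non-informative.

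**Step 1: the stated precision.** 1.96 × √(0.17 × 0.83 / 720) = 0.0274, or ±2.7 points; 0.0274 / 0.17 = 16.1%. The stated figures reproduce.

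**Step 2: Kaplan–Meier with deaths censored.** Fix the actual one-year risk at F = 0.17 and the risk of dying first at D, with constant hazards. The total hazard is −ln(1 − F − D), and the event hazard is λ = F/(F + D) times that. Kaplan–Meier then targets 1 − exp(−λ).

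| D (assumed) | Total hazard | λ | 1 − KM |
|---|---|---|---|
| 3% | −ln 0.80 = 0.2231 | 0.2231 × 17/20 = 0.1897 | 17.3% |
| 5% | −ln 0.78 = 0.2485 | 0.2485 × 17/22 = 0.1920 | 17.5% |
| 8% | −ln 0.75 = 0.2877 | 0.2877 × 17/25 = 0.1956 | 17.8% |
| 10% | −ln 0.73 = 0.3147 | 0.3147 × 17/27 = 0.1982 | 18.0% |

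Defining mortality instead as the one-year death risk in the absence of the event gives nearly the same: +0.25 points at 3%, +0.43 at 5% and +0.88 at 10%.

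**Step 3: crude percentage with a share L lost just after day 30.** Crude = (1 − L) × 17% + L × p30, where p30 is the risk by day 30. With a constant hazard, p30 = 1 − exp(−0.1863 × 30/365) = 1.5%, where 0.1863 = −ln 0.83. If half of all events fall in the first 30 days, p30 = 8.5%.

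| L (assumed) | p30 = 1.5% | p30 = 8.5% |
|---|---|---|
| 10% | 15.3 + 0.15 = 15.5% | 15.3 + 0.85 = 16.2% |
| 20% | 13.6 + 0.30 = 13.9% | 13.6 + 1.70 = 15.3% |

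If loss is instead spread evenly over the year (constant event hazard), the crude figure is 16.2% at 10% loss and 15.3% at 20%. Loss concentrated after day 30 fits this design better. With only two scheduled contacts and an optional diary or app, a patient who misses the one-year call and has no other source was last observed near day 30. Allowing 3% to 10% mortality as well changes the crude figures for loss after day 30 by no more than 0.02 points.

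**Step 4: a rarer outcome.** For an assumed 3% event, Kaplan–Meier is high by 0.05 to 0.16 points at 3% to 10% mortality. The crude figure is low by 0.07 to 0.31 points at 5% to 20% evenly spread loss, and by 0.55 if 20% are lost just after day 30.

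**Step 5: limiting cases.** With no loss the crude percentage is unbiased. With no deaths Kaplan–Meier is unbiased.

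**The case against.** The strongest reply is that the article does not say what happens to deaths or to lost patients. Censoring rules and denominators normally sit in a statistical analysis plan, which is not available here, and the phrase about applicability leaves room to restrict Kaplan–Meier to suitable outcomes. This stands in part: that deaths are censored and lost patients count as event-free is the ordinary reading of the named methods, not something the article states. But the article does name Kaplan–Meier as the means of determining outcome risk, and it does fix the FAS. A choice of method and population is open to comment, whereas a missing detail would not be.

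Second, Kaplan–Meier stands beside the crude percentage and already allows for incomplete follow-up. The article ties risk to the curve rather than to the percentage, and it promises to report completion and reasons for non-completion. Contact with relatives or the primary care doctor and repeated call attempts should also reduce loss. This is fair and softens the crude-percentage half of the point, although those percentages still carry confidence intervals and invite reading as one-year rates.

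Third, the Kaplan–Meier error is small: at most about 1 point over the assumed range, inside the ±2.7 points of planned precision, in patients enrolled with a life expectancy above one year. That also stands.

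Two stronger readings are not supported. A reader might infer that the curves start at the PCI and so need delayed entry. No section says so; the Schedule section states that "The observational period for each patient will begin between 4- and 72-h post-removal of the guiding catheter", and a clock started there has no such problem. A reader might also set the gap between the two estimates against the ±2.7 points. The gap is 18.0 − 15.5 = 2.5 points at 10% loss and 10% deaths, and 18.0 − 13.9 = 4.1 at the extremes. But a gap between two estimators is not the error of either one.

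**Conclusion.** The point holds for bleeding, stroke, MI, repeat PCI and CV death. It does not hold for all-cause death, where nothing competes and Kaplan–Meier is valid under non-informative censoring.

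Around a true 17%, Kaplan–Meier with deaths censored is high by about 0.3 to 1.0 point if 3% to 10% die first. The crude FAS percentage is low by about 0.8 to 1.5 points at 10% loss after day 30, and by 1.7 to 3.1 points at 20%. The crude error is thus the larger of the two, but it passes the planned ±2.7 points only with heavy early loss.

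These sizes rest on assumed loss and mortality, on constant hazards (with a front-loaded variant for the crude figure) and on non-informative loss; informative loss could move Kaplan–Meier either way. It would go too far to say that both planned analyses are certain to be biased, since each error needs deaths or losses whose frequency the article does not give. No stated figure is wrong. This is an improvement worth making because a better-suited estimator is available from data already being collected.

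**What to change.** State in the analysis text that the risk of each non-fatal event and of CV death is the Aalen–Johansen cumulative incidence at day 30 and at one year, with 95% CI. Death from any cause is the competing event for the non-fatal outcomes, and non-CV death is the competing event for CV death. Patients without the one-year contact are censored at their last contact.

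Keep Kaplan–Meier for all-cause death and for any composite that includes it. Continue to show absolute and relative frequencies, but label them as observed counts in the FAS and not as one-year risk. No delayed-entry adjustment is called for.

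The cost is a change of wording and slightly more analysis work. The planned SAS version has standard procedures for this, and no additional data, visits or patients are needed.

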### Ethics approval and consent to participate

This non-interventional study fulfils the requirements of the Directive 2001/83 EC, Guidelines on Good Pharmacovigilance Practices, Directive 95/46 EC and the Declaration of Helsinki and will be conducted in accordance with the respective standard operating procedures of Daiichi Sankyo Europe GmbH (DSE) and/or Clinical Research Organisation in charge of the non-interventional study. The study was approved by the Leading Ethics Committee of University of Cologne on 17th July 2020. The Notification to Bundesinstitut für Arzneimittel und Medizinprodukte was confirmed on 21st July 2020. A site-specific Amendment (Observational Plan and Informed Consent Form) was approved for the study app by the Ethics Committee of Sachsen on 1st June 2021. Written informed consent will be obtained from all patients. If the patient uses the study app, a separate written informed consent for the study app will be obtained.

## Discussion

An antithrombotic therapeutic strategy consisting of an OAC and dual antiplatelet therapy (DAPT; P2Y_12_ inhibitor ± aspirin) is recommended in AF patients undergoing PCI^3^. DAPT is administered with the aim of reducing the risk of post-procedural stent thrombosis during the healing process, as well as other atherothrombotic events; however, the prolonged use of DAPT incurs an increased bleeding risk^23^. Results from the ENCOURAGE-AF study will help understand the current use of antithrombotic therapies (as well as other concomitant medications) in AF patients undergoing PCI during routine clinical practice in Germany. Given the uncertainties around the optimal use and duration of aspirin use following a PCI procedure in AF patients, ENCOURAGE-AF will provide valuable real-world data on the combination and duration of NOACs and antiplatelet agents in patients with AF undergoing PCI. Results from both the AUGUSTUS and ENTRUST AF-PCI trials suggest that concomitant aspirin use is necessary post-PCI, although the optimal duration of concomitant use is not clear yet^13,14^. Investigating the patterns of use of antithrombotics during the first 30-days after the procedure is of particular interest since it is during this time when the risk/benefit trade-off between dual and triple therapy is most important^14^. This is reflected in the most recent ESC 2020 guidelines for patients with AF^3^.

NOAC-based dual therapy is associated with a long-term reduction in bleeding events over the course of the first year of treatment compared with VKA-based triple therapy, however, the short-term use of triple therapy is recommended immediately after a successful PCI to reduce the risk of stent thrombosis^3^. Depending on a patient’s risk of stent thrombosis versus risk of bleeding, the recommended duration for aspirin therapy in parallel with NOAC plus clopidogrel ranges from a maximum of 1 week (bleeding risk > stent thrombosis risk) up to a maximum of 1 month (stent thrombosis risk > bleeding risk)^3^. The ongoing RIVA-PCI study (ClinicalTrial.gov identifier: NCT03315650) will also investigate the real-world use of antithrombotics in AF patients with ACS (or stable disease) undergoing PCI. Adherence to antithrombotic treatment and any complications associated with treatment will be evaluated over 14-months in patients receiving rivaroxaban. Together with the RIVA-PCI registry, ENCOURAGE-AF will expand our knowledge of the patterns of use of antithrombotic therapy in German AF patients with PCI in routine clinical practice. Data from the two non-interventional studies could highlight areas where additional medical education is needed to ensure patients with AF and stent implantation receive optimal clinical care in Germany.

ENCOURAGE-AF will complement the findings of the ENTRUST-AF PCI trial by providing valuable information on the real-world effectiveness and safety of edoxaban in an expanded pool of patients, many of whom may not have otherwise been eligible for entry into the RCT. The study will also provide insights into the quality of life of AF patients following PCI which has not been widely investigated. Moreover, data on the HRU of patients in this specialised patient population will be explored. Insights into the quality of life and health resource utilisation of patients in this specialised population will also be presented and discussed.

The ENCOURAGE-AF study is strengthened by the absence of exclusion criteria, which will avoid selection bias and facilitate the habitual documentation of routine clinical practice. Thus, the prescribing behaviour of physicians will not be influenced by the study. As with all real-world studies, the ENCOURAGE-AF study design has several limitations. Patients participating in competing interventional trials or other edoxaban non-interventional studies are not eligible for inclusion in the study, which might inadvertently lead to some degree of selection bias. Furthermore, the analyses evaluating the effectiveness and safety of edoxaban, as well as effects on patients’ quality of life and HRU, will not include a control group for comparisons, which could lead to bias in the interpretation of the outcomes.

As with all observational studies, ENCOURAGE-AF faces the risk of under-reporting of data, especially due to the long time period between the 1-month and 1-year follow-up time points. This can potentially result in the misclassification of treatment exposure and the incorrect documentation of treatment changes, as well as all other outcomes. While patient medical records, the optional hardcopy patient memory aid, and provision of the structured telephone interview guide for physicians will support the optimal documentation of data between the follow-up time points, their influence on under-reporting relies upon the accuracy and precision of the data recorded. The implementation of a study app that is easy to install and use on older iOS and android smartphones, and which provides immediate email feedback to the study site, is expected to reduce the risk of under-reporting and misclassification. Furthermore, the direct transfer of EQ-5D-5L data from smartphone to the eCRF will reduce the risk of missing data and site data entry errors.

Throughout the study, different methods for categorising bleeding events will be used at baseline compared with the follow-up period due to the different settings in which the data will be collected (hospital versus telephone respectively). During the follow-up, a number of factors may influence the accuracy of the reporting, which relies upon both the physicians’ interviewing techniques and the ability of patients to recall past events precisely, via telephone. The accuracy of reporting could be affected by a patient’s age and/or health status. Thus, in contrast to baseline, when bleeding events are reported in hospital, bleeding events may be under-reported during the follow-up.

## Conclusions

The ENCOURAGE-AF non-interventional study will provide insights into the use of antithrombotics in patients with AF undergoing successful PCI over a year of routine care in Germany. Valuable information regarding the patterns of edoxaban in combination with antiplatelet treatment and other concomitant medications will be obtained for this patient population. Furthermore, the effectiveness and safety of edoxaban, as well as patients’ quality of life and HRU will be evaluated.

